### Study Design and Participants

This study entails cross-sectional, experimental multimodal (clinical, biomechanical, radiological) data collection with multiple conditions and a control group. A total of 25 patients aged 45 to 85 years with unilateral symptomatic rotator cuff tears will be recruited from our clinic. Orthopedic surgeons will inform patients who fulfill the inclusion criteria about the study, and eligible candidates will be contacted. Additionally, 25 asymptomatic controls will be recruited to achieve the same age and sex distribution as in the patient group. Moreover, because of the clinically observed high prevalence of rotator cuff tears in persons without symptoms, we will also recruit 25 sex-matched young asymptomatic controls aged between 20 and 30 years to allow for elucidating the effect of the natural aging process. Detailed inclusion and exclusion criteria for the cohorts are shown in Textbox 1.

Inclusion and exclusion criteria for this study.
**Inclusion criteria**
Patients:Aged 45 to 85 years (n=25)Diagnosed unilateral rotator cuff tear: partial or complete supraspinatus muscle tear, with or without injury to other rotator cuff musclesPrior operative treatment of the ipsilateral shoulder or elbowClinical history or symptoms of the contralateral glenohumeral jointRange of motion <30° in abduction and flexionControl participants:Two age groups: 20 to 30 years (n=25) and 45 to 85 years (n=25)No previous known elbow and shoulder injury or symptomsClinical history of the glenohumeral jointPrior conservative or operative treatment of the shoulder or elbowRange of motion <90° in abduction and flexion
**Exclusion criteria**
Inability to provide informed consentBMI>35 kg/m^2^Neuromuscular disorders affecting upper limb movementAdditional pathologies influencing the mobility of shoulder jointsContraindications for magnetic resonance imaging (eg, neurostimulator and claustrophobia)Prior neuromuscular impairment (eg, stroke)Diagnosed with active rheumatic disorderOther major medical problemsPregnancyCurrently enrolled in another experimental (interventional) protocol

### Experimental Protocol

Each participant will undergo a recruitment and information process before coming to the University Hospital Basel for all planned data collection. Before the assessment, written informed consent will be obtained. Participants will then complete health questionnaires to receive functional scores of the shoulders. Next, fluoroscopic images of a loaded and unloaded 30° shoulder abduction test will be captured, and a 3D motion analysis of the same abduction tests will be performed. Isometric shoulder strength for abduction and internal/external rotation will be assessed with a dynamometer. Finally, magnetic resonance imaging (MRI) images of both shoulders will be taken (Table 1). The estimated total time for each participant is approximately 4 hours. The SPIRIT (Standard Protocol Items: Recommendations for Intervention Trials) checklist, compiled with recommended items to be addressed in a clinical protocol, is provided in Multimedia Appendix 1.

**Table 1 table1:** Schedule of enrollment and assessments.

		Study period	
		Enrollment	Allocation
Time point		Precall	0
**Enrollment**			
	Eligibility screen	✓	
	Informed consent		✓
	Allocation	✓	
**Study groups**			
	Patients		✓
	Control participants (45-85 years)		✓
	Control participants (20-30 years)		✓
**Assessments**			
	Functional scores		✓
	3D motion analysis		✓
	Fluoroscopy		✓
	Dynamometer		✓
	MRI^a^		✓

^a^MRI: magnetic resonance imaging.

#### Functional Scores

Functional scores revealing the patient’s pain, arm range of motion, and ability to perform daily living activities will be assessed using a shortened version of the Disabilities of Arm, Shoulder, and Hand (DASH) questionnaire (QuickDASH) [17] and additional questionnaires, including the Constant Score [18], American Shoulder and Elbow Surgeons Shoulder Score [19], Subjective Shoulder Value [20], and numerical pain rating scale scores. Additionally, participants will complete the EQ-5D-5L [21] questionnaire to assess their general health status.

#### Abduction Test

Participants will be asked to perform a loading/unloading shoulder abduction test until 30°. This test involves abducting the arms to 30° in the scapular plane and then adducting the arms back to the initial (reference) position. All arm movements are performed bilaterally in an upright seated position, with shoulders in the neutral position (hanging arm with thumb toward the front). To control the maximal amplitude of arm abduction, a string is attached to the lower arm and adjusted to the desired maximum position by using a goniometer. Before data collection, participants will be asked to perform exercise movements in the scapular plane. To ensure a comparable speed of movement, verbal commands will be given to the participants.

##### Single-Plane Fluoroscopy

Single-plane fluoroscopic images (Multitom Rax, Siemens Healthineers) will be captured for the following three conditions: without additional weight and in randomized order with 2-kg and 4-kg handheld weights. The rest time between each condition will be at least 30 seconds. Images will be acquired first for the right shoulder independent of the symptomatic side. After a rest period of at least 1 minute, the same tests will be repeated in the same order to obtain images of the left shoulder. The alignment of the scapular plane will be checked by fluoroscopy. Images will be captured with a pulse rate of 10 Hz to minimize radiation exposure. Image dimensions will be calibrated with a reference ball (Ø=25 mm) placed in the field of view.

##### Motion Capture Data

Motion data of this 30° abduction test will be captured with and without additional handheld weights of 1, 2, 3, and 4 kg. The order of the loading conditions will be randomized to minimize fatigue. The task will be interrupted if the participant’s pain exceeds 7 out of 10. Participants will perform 3 trials of each arm movement while kinematic data are collected using a 10-camera Vicon system (Vicon) at a frame rate of 240 Hz. To assess 3D joint angles, retroreflective markers (Figure 1) will be placed on the upper extremity according to the International Society of Biomechanics guidelines [22].

**Figure 1 figure1:**
[figure not shown]
Placement of markers and sensors: (A) anterior and (B) posterior view.

##### Electromyographic Data

Electromyographic data of the infraspinatus, biceps brachii, anterior, middle, and posterior parts of the deltoid, clavicular part of the pectoralis major, latissimus dorsi, and upper trapezius muscles will be recorded during all arm movements. Surface electrodes (Myon AG) will be placed over the corresponding muscles following the guidelines of the SENIAM (Surface ElectroMyoGraphy for the Non-Invasive Assessment of Muscles) project [23] and Criswell [24] (Figure 1). Electromyographic signals will be normalized using the maximal voluntary isometric contraction recorded during the following standard tests (captured during a 5-second trial): empty can, internal rotation 90°, flexion 125°, palm press, and extension [25,26]. Since these tests do not specifically account for the biceps brachii, an additional trial will be captured during maximal contraction against resistance with the elbow flexed at 90°. In the case that a participant cannot reach 90°/125° in flexion or 90° in abduction, these tests will be adapted to the participant’s capabilities by reducing the test angles.

##### Inertial Sensors

Inertial sensor data will also be collected during the loaded and unloaded abduction tests. Additionally, participants will be asked to perform full arm abduction, flexion, and internal and external rotations movements (without additional handheld weight). Inertial sensors (Vicon Blue Trident) will be placed on the participants’ thorax, scapulae, humeri, and forearms [27] (Figure 1). Accelerations and angular velocity will be captured for the various movements.

#### Isometric Shoulder Strength

Shoulder strength will be tested under isometric conditions using a dynamometer (Biodex System 4 Pro, Biodex Medical Systems). Isometric shoulder strength will be assessed for abduction at 10° and 30° in the scapular plane. The participant will be in a seated position with the arm extended in neutral rotation. The protocols comprise 3 repetitions of 5 seconds of pushing and 5 seconds of resting for both abduction angles. Isometric shoulder strength will also be measured for internal and external rotation at neutral rotation in 15° abduction (scapular plane). Participants will be seated with a 90° flexed elbow [28]. The protocol comprises 3 repetitions of 5 seconds of external rotation and 5 seconds of internal rotation with a 5-second rest in between. Both shoulders will be tested in a randomized order. The maximum value of 3 trials will be calculated and recorded as the participant’s maximum isometric strength for each movement.

#### MRI Visualization

MRI will be performed using a 3T scanner (Prisma, Siemens Healthineers) with dedicated shoulder and body array coils. No contrast agent will be administered to the participants. Both shoulders will be scanned. The MRI protocol consists of an axial proton density turbo spin echo (TSE) sequence with fat saturation, a sagittal T1-weighted TSE sequence, a sagittal and a coronal T2-weighted BLADE sequence, and a coronal T1-weighted volumetric interpolated breath-hold examination Dixon sequence (Table 2).

**Table 2 table2:** Characteristics of the MRI^a^ sequences.

MRI sequence	Repetition time/echo time (ms)	Slice thickness (mm)	Field of view (mm)	Matrix
PD^b^ TSE^c^ FS^d^ axial	4500/34	2	140	320 × 320
T1 TSE sagittal	762/11	3	159	384 × 384
T2 BLADE sagittal	4210/72	3.6	160	320 × 320
T2 BLADE coronal	3400/75	3.6	150	320 × 320
T1 VIBE^e^ Dixon coronal	4.04/1.23 (TE^f^1) and 2.46 (TE2)	1.3	238 × 332	184 × 256

^a^MRI: magnetic resonance imaging.

^b^PD: proton density.

^c^TSE: turbo spin echo.

^d^FS: fat saturation.

^e^VIBE: volumetric interpolated breath-hold examination.

^f^TE: echo time.

### Outcome Parameters

The primary and secondary end points are summarized in Textbox 2.

End points of the experimental protocol.
**Primary**
Load-induced glenohumeral translation (liTr) from fluoroscopyLoad-induced muscle activation of the deltoid muscle
**Secondary**
liTr from motion captureAnatomical parametersInjury typeFunctional scores
**Other**
Age, body height, body mass, and sex of the participantIsometric shoulder muscle strengthMuscle cross-sectional area and fatty infiltrationConservative treatment and duration of physiotherapy

#### liTr Measure

Fluoroscopy-based and motion capture–based liTr will be measured (Figure 2).

On the fluoroscopic images, the glenohumeral joint center, humeral shaft, most lateral point of the acromion, and inferior and superior glenoid edges will be registered. The glenohumeral joint center will be determined as the geometric center of a circle comprising the articulating surface of the humeral head [29-32]. Hence, glenohumeral translation during arm abduction and adduction will be measured as the inferior-superior component of a glenoid coordinate system [33] (Figure 2A). The arm abduction angle will be measured as the angle between a line passing through the glenohumeral joint center, the humerus shaft midpoint, and the vertical line.

Glenohumeral translation will also be assessed using instrumented motion analysis. The calibrated scapular and humeral landmarks will be used along with equations outlined by the International Shoulder Group [34] and the functional joint center method to determine the instant glenohumeral joint center within the humerus reference system. The vertical distance from the glenohumeral joint center to the acromion marker will be calculated for a neutral trial and with the arm in 30° shoulder abduction for each loading condition. Motion capture–based liTr will be calculated for each participant as the differences in the distance between the glenohumeral joint center and the acromion under different loading conditions (Figure 2B).

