### Statistics and Determination of Sample Size

All study-related data will be entered into and stored using a web-based Research Electronic Data Capture (REDCap; Vanderbilt University) system [50,51]. All statistical analyses will be performed in R statistical software [52]. Overall, 25 patients with 1 symptomatic shoulder with a rotator cuff tear, 25 age- and sex-matched asymptomatic control participants, and 25 sex-matched young control participants will participate in this study. This means that a total of 150 shoulders will enter the analysis. Comparisons between the fluoroscopy-based liTr and motion capture–based liTr will be made. Reproducibility and agreement will be assessed by the mean and standard deviation of differences and Bland-Altman plots. Precision in estimating the liTr will be assessed by average relative standard errors and *R*^2^ values from a global model. Potential deviations from a linear relationship will be assessed by random effects models for a quadratic term. The influence of covariates on the liTr and the biological variation of liTr will be assessed by mixed models applied to the original glenohumeral translation measurements with the liTr as a random effect. Dependence between the shoulders will be considered by bivariate random effects.

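### The two liTr measures set against each other for agreement are defined on different axes and reference points; a like-for-like comparison should be added so that definition and measurement error can be told apart

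*Protocol article*

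**What the plan says.** All references are to the protocol article.

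- **Fluoroscopy (liTr Measure).** The humeral-head centre is located by fitting a circle, and "glenohumeral translation during arm abduction and adduction will be measured as the inferior-superior component of a glenoid coordinate system". That frame turns with the scapula. The most lateral acromion point is registered on the same images. The arm angle is taken from a line through the joint centre, "the humerus shaft midpoint, and the vertical line".
- **Motion capture (liTr Measure).** Landmarks and a functional method are used "to determine the instant glenohumeral joint center within the humerus reference system". Then: "The vertical distance from the glenohumeral joint center to the acromion marker will be calculated for a neutral trial", and also with the arm at 30°. Motion-capture liTr is the "differences in the distance between the glenohumeral joint center and the acromion under different loading conditions".
- **Comparison (Statistics and Determination of Sample Size).** The two versions of liTr are to be set against each other, and the method is named: "Reproducibility and agreement will be assessed by the mean and standard deviation of differences and Bland-Altman plots". This serves research question 7 in the Introduction, on whether the two methods are comparable.
- **Stated limitation (Discussion).** The one reason given why the two recordings might differ is that they are not simultaneous, so the movement may be executed differently.

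**The concern.** Limits of agreement describe measurement error only when both methods aim at the same quantity. Here the axis differs (glenoid against vertical), as does the reference point (glenoid against acromion marker). No common sign is stated: a superior shift of the humeral head raises a glenoid-axis coordinate that is positive upwards, but shortens the distance to the acromion.

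If load changes scapular orientation at the same arm angle, the vertical distance can change while the glenoid-axis value does not. The string that limits abduction fixes the arm's amplitude, not how that amplitude is shared between scapula and humerus.

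At stake is the answer to research question 7. Wide limits or a bias could be blamed on motion-capture error, or on differences in movement execution, when part of the cause is definitional. Motion-capture liTr is also a listed secondary endpoint.

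**Working it through.** The protocol gives no figure for agreement, so there is nothing to reproduce. The check is plane geometry on the two definitions.

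**Inputs from the protocol (Sample Size Calculation).** Measurement-error SD of liTr 0.16 mm; detectable liTr difference 0.8 mm. Both serve only as yardsticks.

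**Assumed inputs, not in the protocol.** Acromion marker *x* = −10 to +20 mm lateral and *y* = 25 to 45 mm superior to the joint centre, in the scapular frame; scapular tilt φ = 0 to 10°; load-induced change in scapular rotation *d* = 1 to 5°.

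**1. Vertical distance.** V(φ) = *y* cos φ + *x* sin φ. With zero translation along the glenoid axis, a rotation *d* between load conditions changes motion-capture liTr by V(φ + *d*) − V(φ). For small *d* this is roughly lever × *d* in radians, where lever = *x* cos φ − *y* sin φ. Fluoroscopic liTr changes by 0 in this ideal case.

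**2. Per degree (1° = 0.01745 rad).**
- Largest in the range: *x* = 20, φ = 0, lever 20 mm, 20 × 0.01745 = 0.35 mm.
- Opposite sign: *x* = −10, *y* = 45, φ = 10°, lever −9.85 − 7.81 = −17.66 mm, giving −0.31 mm.
- Small: *x* = 10, *y* = 35, φ = 10°, lever 9.85 − 6.08 = 3.77 mm, giving 0.07 mm.
- Near zero: *x* = 10, *y* = 45, φ = 10°, lever 9.85 − 7.81 = 2.03 mm, giving 0.04 mm.

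One degree reaches 0.16 mm only when the lever is about 0.16 / 0.01745 = 9.2 mm or more in size.

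**3. Larger rotations, exact formula.** In size: 0 to about 0.7 mm for 2°, 0 to about 1.0 mm for 3°, and 0 to about 1.7 mm for 5°.

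**4. Effect on limits of agreement.** Assume independent error of SD 0.16 mm in each method. The half-width is 1.96 × √(2 × 0.16²) = 0.44 mm. With a 10 mm lever and a between-shoulder SD of load-induced rotation *s*, it becomes 1.96 × √(2 × 0.16² + (10 × 0.01745 × *s*)²):

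| *s* (degrees) | artefact SD (mm) | half-width (mm) |
|---|---|---|
| 0 | 0 | 0.44 |
| 1 | 0.17 | 0.56 |
| 2 | 0.35 | 0.82 |
| 3 | 0.52 | 1.12 |

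**5. Scale.** A true translation *t* along the glenoid axis changes the vertical distance by −*t* cos φ. Since cos 10° = 0.985, the loss of scale is trivial; only the sign matters.

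**6. Repair.** Let M be motion-capture liTr, G fluoroscopic liTr on the glenoid axis, and F the same fluoroscopic images read as a vertical joint-centre-to-acromion change, all with one sign. Then (M − G) − (M − F) = F − G. The gap between the two comparisons is the definitional part, obtained from the same images.

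**The case against.** - **The mechanism needs a laboratory vertical.** The construction is in Figure 2B, which is not available here, and in cited equations. A scapula-fixed vertical would remove the rotation term. This stands as a limit. The laboratory reading is still the natural one: the text names no scapular axis, and the section's other use of the term is the reference line for the arm angle. The differing reference points and unstated sign would remain in any case.
- **The size is conjecture.** The protocol gives neither marker offsets nor load-induced rotation, and some plausible geometries give almost nothing. Rotation common to loaded and unloaded trials largely cancels. This stands. A reader might infer that scapular rotation is bound to appear as method disagreement; the documents support only that it can.
- **The yardsticks are loose.** The 0.16 mm refers to a sphere method at 3 kg against no load, with the modality unstated, and 3 kg is not imaged by fluoroscopy in this study. The 0.8 mm is a detectable difference, not an agreement criterion. Both points stand.
- **Repeated measurements.** A reader might also infer that the limits of agreement are invalid because two shoulders and several loads per person are pooled. The protocol nowhere says they are pooled; analysis by side or load fits the text equally well, and bivariate random effects are named for dependence between shoulders. That charge is not shown.
- **The direct comparison is legitimate.** Whether motion capture can stand in for the primary fluoroscopic measure is a fair practical question, and sensitivity to scapular rotation would be a real weakness of motion capture. This stands, and is why the planned comparison should be kept.
- **Sign is a coding matter.** True, but it should be stated, since a mean difference cannot be interpreted without it.

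**Conclusion.** The point holds as a cheap improvement. The mismatch of axis and reference point is explicit in the text, and so is the use of agreement statistics on the two measures. Followed as written, the analysis cannot tell how much of any disagreement comes from definition. If the vertical is the laboratory vertical, the rotation artefact is about 0 to 0.35 mm per degree under the assumed offsets and tilt, so it may be negligible or may exceed the 0.16 mm error SD; the documents cannot settle which. The consequence is confined to research question 7 and the interpretation of the secondary motion-capture liTr. Fluoroscopic liTr, the primary endpoint, and Hypothesis 1 are untouched.

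**What to change.** 1. State the axis, reference point and direction of subtraction for each liTr measure, with one sign convention (for example, superior translation positive).
2. Keep the planned fluoroscopy against motion-capture comparison, described as a comparison of two differently defined quantities.
3. Add a like-for-like agreement analysis at the shared loads of 0, 2 and 4 kg. Either compute on fluoroscopy the vertical distance from joint centre to lateral acromion, in neutral and at 30°, or project the motion-capture joint centre on a scapula-fixed axis.
4. Interpret the difference between the two comparisons as the definitional part of the disagreement, and what remains in the like-for-like analysis as measurement error, movement execution and landmark mismatch.

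Cost: no new data, a little extra computation and a few sentences of text. With the fluoroscopic option the match is imperfect, because a projected bony point and a skin marker on the acromion are not identical; that residual mismatch should be acknowledged.

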**Figure 2 figure2:**
[figure not shown]
Load-induced glenohumeral translation (liTr). (A) Fluoroscopy-based and (B) motion capture–based measurements. GH: glenohumeral joint center.

#### liMA Measure

First, an independent component analysis–based filtering will be applied to the electromyographic data to remove electrocardiogram contamination [35]. Then, additional noise artifacts will be removed by a modified bandpass filter of 10 Hz to 450 Hz [36]. For each muscle, liMA will be computed for each loading condition of the abduction test as the root mean square of the electromyographic signal during the loaded arm positions relative to the root mean square of the electromyographic signal during the unloaded arm position [37]. Electromyographic data will be normalized to the maximal voluntary isometric contractions for visual presentation of the electromyographic trajectories.

#### Critical Shoulder Angle

Participants’ critical shoulder angle will be measured on an anterior-posterior double-obliquity fluoroscopy image of the shoulder. This is defined as the angle subtended by a line parallel to the glenoid and a line through the inferior-lateral edge of the glenoid and the inferior-lateral edge of the acromion [5]. The critical shoulder angle has been shown to be reproducible and significantly greater in patients with rotator cuff tears than in the general population [5]. High angles (>35°) have been associated with rotator cuff tears and greater joint instability [38]. Although it can be assumed that there are no side-to-side differences in the critical shoulder angle [39], it will be measured for both shoulders of all the participants (left and right).

